#### Recruitment

Participants in the AN and CC groups are recruited through the Department of Child and Adolescent Psychiatry, Psychosomatics and Psychotherapy of the LMU University Hospital Munich. Potentially eligible in- and outpatients and their parents/legal custodians are approached by a member of the study team and provided a comprehensive explanation of the study procedures. Participants in the HC group are recruited via previous studies in which they had participated as healthy controls. Families receive a letter with information about the study and an invitation to participate. Participants receive a reimbursement of €30 as shopping vouchers (e.g., for Amazon).

#### Psychopathology assessment and self-report data

All participants undergo extensive diagnostic assessment before inclusion in the study. A standardized, semi-structured diagnostic interview [Kinder-DIPS; 65, 66] is conducted to assess psychiatric diagnoses. The Kinder-DIPS is a well-established German diagnostic interview that allows diagnosis of a wide range of psychiatric axis I disorders according to DSM-5 [1] with good interrater-reliability [66]. The interviews are conducted and evaluated by trained interviewers. Interrater-reliability will be determined for 25% of the participants by an independent researcher re-rating audio recordings of the diagnostic interviews (pre-defined criteria: lifetime-diagnoses of AN, major depression, social phobia, or generalized anxiety disorder). In the AN and CC groups the diagnostic interview serves to confirm diagnoses of AN, major depression, or anxiety disorders and to detect comorbidities. In the HC group the interview helps to rule out the presence of any current or past mental disorders. In addition, ED symptoms are assessed using the Eating Disorder Inventory [EDI-2; 67], depressive symptoms are assessed using the Beck Depression Inventory [BDI-II; 68], and the anxiety symptoms are measured using the State-Trait Anxiety Inventory [STAI; 69]. Height and weight (to calculate body mass index, BMI) of AN patients and CC inpatients are obtained from their physicians while HCs and CC outpatients are weighed and measured in our laboratory. Furthermore, sociodemographic data, self-esteem [Rosenberg Self-Esteem Scale, RSES; 70], body dissatisfaction [Body Shape Questionnaire, BSQ; 71], and social appearance anxiety [Social Appearance Anxiety Scale, SAAS; 72, 73] are assessed via questionnaires.

### Study procedure

For participating adolescents, the study consists of two sessions. In the first session, the diagnostic assessment takes place, i.e., IQ is assessed with the CFT 20-R [62] and the diagnostic interview [Kinder-DIPS; 65, 66] is conducted. If the adolescent is eligible for inclusion in the study, she is invited to the second session that takes place approximately one week later. In that session, cognitive biases are assessed using an experimental paradigm. Between the two sessions, participants are asked to fill out some of the questionnaires (sociodemographic questionnaire, EDI-2, Trait Version of the STAI, RSES, BSQ, SAAS). The remaining questionnaires (BDI-II, State Version of the STAI) are filled out at the beginning of the experimental session.

### Experimental paradigm

Cognitive biases are measured with a computerized version of the SST [adapted from 50, 54]. This task was originally designed to assess interpretation biases [51] but is administered during eye-tracking in the present study to enable simultaneous assessment of attention biases. It is followed by an incidental free recall test of the previously constructed interpretations that assesses memory biases [cf. 50].

The task consists of three types of trials: (1) ED-related (EDR) emotional trials that allow the assessment of cognitive biases for ED-related information, (2) non-ED-related (NED) emotional trials that allow the assessment of non-ED-specific cognitive biases, and (3) neutral trials that will not be analyzed.

#### Stimuli

Stimuli consist of 70 scrambled sentences: 28 EDR emotional sentences (e.g., “my fat bottom find attractive I”), 28 NED emotional sentences (e.g. “total I winner a loser am”), and 14 neutral sentences (e.g., “I exciting watching funny movies like”). All sentences contain six words and have two possible solutions. Emotional sentences include one positive target word (“attractive”, “winner”) which can be used to build a positive solution (“I find my bottom attractive”, “I am a total winner”) and one negative target word (“fat”, “loser”) which can be used to build a negative solution (”I find my bottom fat”, “I am a total loser”). The EDR emotional stimuli are based on the stimulus set developed by Brockmeyer et al. [12], which was adapted and extended. They consist of self-referent sentences related to the evaluation of one’s body and physical appearance. The NED emotional stimuli are based on the original stimulus set developed by Wenzlaff and Bates [51], which was translated into German [74], extended, and adapted. They consist of self-referent sentences involving self-evaluation that is not related to body, weight, or appearance. A similar stimulus set has already used in previous studies in youth [54, 55]. Neutral sentences are also self-referent but do not involve any positive or negative evaluation of oneself. As such, both solutions are emotionally neutral. The stimuli are constructed in such a way that they include no negations and the target words are emotional words corresponding in valence to the respective solution (i.e., positive words correspond to positive solutions and negative words correspond to negative solutions). Target words are matched for length and frequency in the German language across the stimulus set.^4^ In line with Everaert et al. [50], word position within each sentence is randomized with target words not allowed next to each other or in the first or last position and counterbalanced whether the positive or negative target word is presented first.

#### Procedure

The trial procedure is depicted in Fig. 1. The experiment is presented using Experiment Builder 1.10 [75]. Each trial starts with a fixation cross presented for 500 ms on the left side of the screen. After that, the stimulus display appears, consisting of six words in scrambled order presented at the center of the screen on a single line. Stimuli are presented in white Arial font size 20 on black background. Participants are instructed to read the words, mentally form a grammatically correct five-word sentence as quickly as possible, and click on the mouse button as soon as they did so to continue to the response part of the trial. The scrambled sentence is presented for a maximum of 8000 ms; if no mouse click occurs during that time the response part is omitted and the next trial begins. In the response part, five boxes appear below the scrambled sentence and participants are required to build the sentence they had mentally formed by ordering the words into the five boxes via mouse click.

**Fig. 1 Fig1:**
[figure not shown]
Example of a NED emotional SST trial and overview of the experimental procedure

Trials are randomly divided into seven blocks of ten, each containing four ED-related emotional trials, four non-ED-related emotional trials, and two neutral trials. Trials are presented in a random order within blocks and blocks are also presented in a random order. Before the first block, participants complete five neutral practice trials to familiarize themselves with the task. Similarly to earlier studies [e.g., 50, 52] a cognitive load procedure is included to prevent deliberate response strategies: Before each block, a 5-digit number is presented for 5000 ms which has to be memorized and recalled at the end of the block.

After the SST a filler task (an unrelated task consisting of watching pictures) lasting approximately 15 min is administered [e.g., 76]. Filler tasks serve to displace the content from the working memory so participants have to retrieve the content from episodic memory during a subsequent free recall [77]. Afterwards an incidental free recall test is administered. Participants are asked to recall as many of the sentences they had previously formed as possible and write them on a piece of paper. Up to ten minutes are allowed for this task but the participants are not informed about the time limit.

Attention biases are assessed via eye movement registration during the stimulus display parts of the trials while interpretation biases are derived from the behavioural results, i.e., the sentences the participants construct in the task. Memory biases are measured with the free recall test at the end of the experimental paradigm (see Fig. 1).

#### Eye-tracker

Eye movements are registered with an EyeLink 1000 Plus Desktop mounted eye-tracker which uses infrared video-based tracking technology [78]. Participants are seated in front of a 15-inch monitor (1024 × 768 pixel resolution) on which the experiment is presented. Viewing is binocular while eye movements are registered from the dominant eye with a sampling rate of 1000 Hz. A forehead and chin rest are used to minimize head movements and keep the viewing distance constant at 65 cm. Lighting of the room is kept constant for all participants. Before the task starts, a 9-point calibration and validation procedure is conducted and calibration is accepted if the average error is less than 0.5° of visual angle and the maximum error is less than 1° of visual angle.

Eye movement events are detected using a velocity- and acceleration-based saccade detection method with saccades defined, in line with previous studies [e.g., 79–81], as events with a velocity above the threshold of 30°/s or an acceleration above the threshold of 8000°/s^2^. Gaze positions that are stable within 1° of visual angle for at least 60 ms are defined as fixations [in line with e.g., 82, 83].

### Analyses

#### Data processing and outcome variables

Participants’ responses (i.e., the sentences they built in the SST and the sentences they remembered in the free recall test) will be rated as correct or incorrect according to predefined criteria by two independent raters. Trials in which no grammatically correct sentence is built (time-out or incorrect sentence) will be excluded from the analyses. Participants with a correct sentence rate of three standard-deviations (*SD*) below the mean (in the SST) will be identified as outliers in terms of accuracy [e.g., 55] and excluded from all analyses.

For analysis of attention biases, we will additionally exclude trials with poor eye-tracking data quality [i.e., trials in which the total dwell time is less than 75% of the presentation time due to excessive blinks, missing data, or participants not looking at the screen; 79, 80]. Subsequently, participants with insufficient remaining trials [less than 75%; e.g., 80] and participants with systematic calibration errors (identified by visual inspection) will be excluded from the analysis of attention biases. Attention bias scores will be calculated by dividing the percentage of dwell time on negative target words (i.e., on the areas of interest around those words) by the sum of percentage of dwell times on negative and positive target words, so that a higher value indicates a more negative attention bias [similar to 50]. Separate scores for EDR and NED sentences will be calculated, resulting in an AB_EDR_ and an AB_NED_ score.

For analysis of the interpretation bias, the correctly unscrambled emotional sentences will be categorized as either positive or negative. Two interpretation bias scores will be calculated: IB_EDR_ reflects the proportion of negatively resolved sentences from the total number of correctly resolved EDR sentences while IB_NED_ reflects the proportion of negatively resolved sentences from the total number of correctly resolved NED sentences [50].

For analysis of memory biases, memory bias scores (MB_EDR_ and MB_NED_) will be calculated similarly: as the proportion of correctly remembered negative sentences from the total number of correctly remembered EDR or NED sentences [50], respectively.

Thus, two relative bias scores emerge on each level of information processing: one reflecting bias for *negative versus positive ED-related information* (AB_EDR_, IB_EDR_, and MB_EDR_) and one reflecting bias for *negative versus positive non-ED-related emotional information* (AB_NED_, IB_NED_, and MB_NED_).

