## Background

Anorexia nervosa (AN) is a mental disorder characterized by significantly low body weight, intense fear of gaining weight and body image disturbance [1]. The disorder primarily affects adolescent girls and women with a lifetime prevalence of between 0.9% and 2.2% [2, 3]. Onset of the disorder is often in adolescence and young adulthood: roughly 40% of patients are 15–19 years old [3]. AN is a severe and highly debilitating disorder, with the highest mortality rate of all mental disorders [4, 5] and a relatively poor long-term prognosis: less than half of patients recover completely and about 20% of cases take a chronic course [6, 7].

In addition to the core symptoms, patients with AN often show dysfunctional cognitions regarding disorder-related information, i.e., information related to food, body, and weight [e.g., 8–10]. These dysfunctional cognitions manifest themselves, for example, as cognitive biases at different levels of information processing: attention to, interpretation of, and memory for eating disorder (ED)-related information. Attention biases are defined as tendencies to focus attention on information that is consistent with one’s dysfunctional cognitions [e.g., 11]. For example, to attend more to one’s unattractive body parts rather than the garment itself when trying on a new dress. Negative interpretation biases are tendencies to attribute negative rather than neutral or positive meanings to ambiguous information [e.g., 12]. For example, interpreting the shop assistant’s suggestion to try on another dress as “you’re too fat for that dress” instead of “another colour might suit you better”. Memory biases, in turn, refer to tendencies to remember information consistent with one’s dysfunctional cognitions better than other information [e.g., 13], e.g., remembering situations in which someone said something negative about one’s weight or shape better than situations in which one received a compliment. These cognitive biases are not only correlates of the disorder but are considered to play an important role in both the development and maintenance of AN [e.g., 8–11].

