#### Sample size

As research on cognitive biases in adolescents with AN is very scarce we had to rely on results in adult AN samples for our sample size calculation [via G*Power; 63]. The aim of the present study is to investigate whether adolescents with AN show attention, interpretation, and memory biases. With regard to attention biases for ED-related information (i.e., body-related stimuli), a meta-analysis [15] reported a medium-sized effect (Glass' *g* = 0.5) for the group difference between patients with AN and HCs. Regarding attention biases for non-ED-related information, studies reported small [*d* ≤ 0.3; 26–28, 31, 32] to large [*d* ≥ 1.1; 23, 24] effects. With respect to interpretation biases, large effects (*d* ≥ 1.5) were reported for ED-specific [12, 18] as well as non-ED-specific biases [29]. A large effect was also reported for ED-specific memory biases [*d* = 0.8; 21]. In order to detect medium to large (*η*_*p*_^2^ = 0.08)^3^ main effects of the factor Group with an α of 0.05 and a power of 0.80 in a multi-factorial analysis of variance (ANOVA) with three groups, a sample size of *N* = 87 subjects is required. Furthermore, we want to examine to what extent these cognitive biases are specific for ED-related information and expect specificity of biases to translate as Group × Content interactions in the multi-factorial ANOVAs. None of the previous studies reported an effect size for such an interaction. If a small to medium-sized effect is assumed (*η*_*p*_^2^ = 0.03), a sample size of *N* = 81 subjects is necessary to detect the interaction. Since effects might be smaller in adolescent patients and experience shows that some subjects will have to be excluded from the analysis due to insufficient data quality in the experimental paradigms that we apply (see below for criteria), we aim for a total sample size of at least 105 subjects, *n* = 35 per group to ensure sufficient power.

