#### Analyses of hypotheses

Statistical analysis of the data will be performed using IBM SPSS Statistics. Group differences in demographic and clinical characteristics (age, IQ, body-mass-index as well as ED, depression, and anxiety symptoms) and other questionnaire scores (self-esteem, body dissatisfaction, and social appearance anxiety) will be examined using univariate ANOVAs with the between-subjects factor Group (3: AN, CC, HC) and follow-up *t*-tests. The hypotheses will be addressed with separate analyses for attention, interpretation, and memory biases. Repeated-measures ANOVAs on bias scores will be performed with within-subject factor Content (2: EDR, NED) and between-subjects factor Group (3: AN, CC, HC). Significant main effects and interactions will be followed up by post-hoc ANOVAs and *t*-tests. We expect our hypotheses (hypothesis 1 regarding ED-related biases: AN > CC = HC; hypothesis 2 regarding non-ED-related biases: CC ≥ AN > HC) to translate as Group × Content interactions in the ANOVAs and corresponding results in the post-hoc tests. Associations between bias scores and psychopathology (questionnaire measures) will be assessed via Pearson’s correlations. For all analyses, the significance level will be set to *p* = 0.05 (two-tailed) and adjusted according to the Bonferroni–Holm procedure [85] when multiple post-hoc comparisons are performed. Effect sizes will be reported for all significant effects: *η*_*p*_^2^ and *η*_*G*_^2^ for ANOVA effects and Cohen’s *d*_*s*_ for between-group *t*-tests, as suggested by Lakens [86]. In addition to testing our hypotheses, we will explore to what extent cognitive biases are related to participants’ psychopathology by calculating correlations between bias scores and ED, depression, and anxiety symptoms as well self-esteem, body dissatisfaction, and social appearance anxiety.

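### The memory-bias score is confounded with interpretation bias, because it ignores how many negative and positive sentences each girl formed and so had available to recall

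*Protocol article*

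**What the plan says.** The Background section says that memory biases "refer to tendencies to remember information consistent with one’s dysfunctional cognitions better than other information". That is a comparison of how well two kinds of material are retained.

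The recall task, under Experimental paradigm (Procedure), draws on the participant's own output: "Participants are asked to recall as many of the sentences they had previously formed as possible". Under Data processing and outcome variables, the interpretation score for ED-related content "reflects the proportion of negatively resolved sentences from the total number of correctly resolved EDR sentences", with a matching score for non-ED-related content. The memory score is built the same way, "as the proportion of correctly remembered negative sentences from the total number of correctly remembered EDR or NED sentences".

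Under Analyses of hypotheses, "The hypotheses will be addressed with separate analyses for attention, interpretation, and memory biases", each a Group × Content repeated-measures ANOVA. IB does not enter the memory analysis, and nothing in the analysis sections adjusts MB for the number of negative sentences formed. The Reliability section restricts analysis and reporting to scores with a Spearman-Brown corrected split-half reliability above 0.7.

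**The concern.** The score does not measure what the Background defines. A girl who formed mostly negative sentences will recall mostly negative sentences even if she retains both kinds equally well. The Sample size section leads one to expect a large group difference in formation: "With respect to interpretation biases, large effects (*d* ≥ 1.5) were reported for ED-specific" and for non-ED-specific biases, in adult samples.

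Memory is one of the three levels on which the study expects to show bias. The test of specificity is exposed in the same way, since a Group × Content interaction in IB reappears in MB. The Discussion wants the results to help later studies choose which biases to target. A memory finding that only restates the interpretation finding could misdirect that choice, and no other planned analysis would reveal it.

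**Working it through.** **1. The plan's own figures.** The article gives no figure for the dependence of MB on IB. Its sample sizes, "with an α of 0.05 and a power of 0.80 in a multi-factorial analysis of variance (ANOVA) with three groups", do reproduce with two measures per girl and an assumed correlation of 0.5.
- Group effect: f² = 0.08/0.92 = 0.0870; λ = 0.0870 × 87 × 2/1.5 = 10.1; power 0.804 at N = 87.
- Interaction: f² = 0.03/0.97 = 0.0309; λ = 0.0309 × 81 × 2/0.5 = 10.0; power 0.800 at N = 81.

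The issue is what MB measures, not the study's size.

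**2. Expected MB without memory bias.** Suppose a girl forms n correct sentences of one content, K of them negative, and recalls some of them regardless of valence. The number of negatives recalled is hypergeometric, so E[MB] = K/n = IB. For 12 negative of 24 this is 0.50; for 6 of 24 it is 0.25. This step needs no outside figure. The equality is in expectation; an individual's MB scatters around her IB because few sentences are recalled.

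**3. Size of the carry-over.** From the documents: "28 EDR emotional sentences" and as many non-ED-related, 35 per group, IB d of 1.5 or more in adults. Assumed: 24 of 28 sentences correct, mean propensity to form a negative sentence 0.55 (AN) and 0.25 (HC), between-person SD 0.18, and 3–12 sentences recalled per content.

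The mean of p(1−p) within a group is μ(1−μ) − SD²: 0.2475 − 0.0324 = 0.2151 for AN and 0.1875 − 0.0324 = 0.1551 for HC, averaging 0.1851.
- IB: variance 0.0324 + 0.1851/24 = 0.0401, so d = 0.30/0.200 = 1.50.
- MB from r recalled sentences: variance 0.0324 + 0.1851/r. For r = 5 this is 0.0694, so d = 0.30/0.263 = 1.14.

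An AN mean of 0.40 instead of 0.55 gives an IB d of about 0.75.

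Simulation lets the recall count vary, which lowers d slightly. All rows have no memory bias; tests are two-sided AN–HC at 0.05, unadjusted.

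| Mean recalled per content | 3 | 5 | 8 | 12 |
|---|---|---|---|---|
| MB d, formula (IB d 1.5) | 0.98 | 1.14 | 1.27 | 1.37 |
| MB d, simulated | 0.91 | 1.08 | 1.24 | – |
| MB significant, IB d about 1.5 | 94% | 99% | >99% | about 100% |
| MB significant, IB d about 0.76 | about 45% | 59% | 71% | about 78% |
| Significant and reliability > 0.7, IB d about 1.5 | 3% | 3% | 29% | 89% |
| Significant and reliability > 0.7, IB d about 0.76 | 0.5% | 0.6% | 6% | 41% |

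**4. Stricter test, other spreads.** A separate simulation used SD 0.20, a 1.5 SD difference in propensity (observed IB d about 1.4) and the strictest Holm step, 0.05/3 = 0.0167. MB is significant in 85%, 96%, 99% and 99.7% of studies at 3, 5, 8 and 12 recalled. For a propensity difference of 0.8 SD the range is 32–65%, for 0.5 SD 12–28%, and for none 1.3–1.8%, which is nominal. For the 1.5 SD difference, the share that is both reliable enough and significant depends strongly on the spread:

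| SD | 3 | 5 | 8 | 12 |
|---|---|---|---|---|
| 0.15 | 0% | 0% | 2% | 30% |
| 0.20 | 3% | 11% | 52% | 96% |
| 0.25 | 38% | 72% | 98% | 100% |

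**5. What makes MB reliable.** At SD 0.20 and 12 recalled, with neither memory bias nor a group difference in IB, MB still has a mean split-half reliability of 0.74 and passes in 78% of studies. Stable individual differences in IB produce that reliability. With the 1.5 SD difference, MB passes in 53% and 97% of studies at 8 and 12 recalled, and is both passed and significant in 52% and 96%.

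**6. Conditional scores.** In the same no-memory-bias simulations at 0.05, MB minus IB rejects in about 3–7% of studies, and recall rate of negatives minus recall rate of positives in 4–7%.

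**The case against.** The strongest objection is the reliability rule. A reader might infer that a spurious memory bias will be reported, or is nearly guaranteed. The document does not support that: a score at or below 0.7 is not analysed, and with sparse recall and modest spread MB would usually be dropped. This stands, and the rates without the rule should not be quoted alone. It is no remedy, though, because the rule checks consistency, not what the score measures.

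Second, recall counts, base rate and spread are all assumed, and the d of 1.5 comes from adults; the Sample size section itself allows for smaller effects in adolescents. This also stands. At IB d of 0.5 to 0.8 the artefact is a substantial risk, not a near certainty. The identity in step 2 depends on none of these inputs.

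Third, a reader might conclude that MB says nothing about memory. That goes too far: MB would also reflect a true memory bias if there were one. The fault is that the two sources cannot be told apart.

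Finally, the score follows a cited study. Precedent is a reason to keep it for comparability, but it does not alter the arithmetic. Attention and interpretation scores are unaffected.

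**Conclusion.** The concern holds as confounding: MB as defined cannot separate memory bias from interpretation bias, and it departs from the article's own definition of memory bias. That conclusion follows from the definitions alone.

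Its practical size is conditional. Without the reliability rule, an unadjusted AN–HC difference in MB appears in about 94–100% of studies at IB d about 1.5 and about 45–78% at d about 0.8, with no memory bias. With the rule, the risk at SD 0.18 and d about 1.5 runs from about 3% at 3 or 5 recalled to 89% at 12, and it is higher with more spread between girls. The document does not fix where in that range the study falls. Under the no-memory-bias assumption, an MB result that passes the rule owes its reliability to IB.

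**What to change.** Make the main memory analysis conditional on what each girl formed, by one of two routes.

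- **Score.** Use MB minus IB for the same content in the planned Group × Content ANOVA. This is the smaller change. Its nominal error rate was checked for the case of no valence effect on recall in any group.
- **Model.** Fit a sentence-level logistic mixed model with one row per correctly formed emotional sentence and recalled (yes/no) as outcome. Use fixed effects Valence × Group × Content, participant and sentence intercepts, and a by-participant valence slope. Test Valence × Group within each content, because the hypotheses are content-specific, plus the three-way term. Without the slope, the Valence × Group test is too liberal if girls differ in their valence effect.

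State how girls who recall nothing of a content, or who formed no negative or no positive sentences, are handled, and how the 0.7 reliability rule applies to the new analysis. Keep the present MB as a secondary score, described as not independent of IB.

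The cost is wording and modest analysis. The article describes data collection as ongoing, and the design already rates both formed and recalled sentences, so no new measurements are needed. The downside is a noisier outcome, because few sentences may be recalled.
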